## Abstract

**Introduction:** Treatment of autoimmune pancreatitis (AIP) is based solely on consensus and has yet to become standardized. Consequently, therapeutic regimens vary greatly between countries and centers, and largely depend on the experience of the physician. At this moment, the optimal regimen for inducing disease remission and preventing relapse is unknown.

**Objectives:** The primary objective of this study is to describe current treatment regimens used in Europe, and to compare their effectiveness in inducing remission and preventing and treating relapse. The secondary objectives are: to identify risk factors for relapse; to assess the diagnostic accuracy of the Unified-AIP criteria; to assess the performance of the M-ANNHEIM score for predicting relapse; and to assess long-term outcomes including pancreatic exocrine insufficiency and pancreatic cancer.

**Methods:** This is an international, retrospective, observational cohort study, performed in over 40 centers from 16 European countries. Eligible are all patients diagnosed with AIP from 2005 onwards, regardless of the used diagnostic criteria. Data on study subjects will be retrieved from the hospital's electronic medical records and registered with a standardized, web-based, electronic case report form (eCRF). To compare the effectiveness of treatment regimens in inducing remission, preventing relapse, and treating relapse, subjects will be stratified in groups based on: type of therapy; initial therapy dose; cumulative therapy dose; therapy tapering speed and duration; and having received maintenance therapy or not.

**Ethics and Dissemination:** Ethical and/or institutional review board approvals are obtained by all participating centers according to local regulations. The study complies with the General Data Protection Regulation (GDPR). All manuscripts resulting from the study will be submitted to peer-reviewed journals.

**Conclusion:** This is the first pan-European retrospective registry for AIP. It will produce the first large-scale data on treatment of European patients with AIP, providing answers on the use and effectiveness of treatment regimens. In the future, this collaboration may provide a network for continuation into a prospective European registry.

## Introduction

Autoimmune pancreatitis (AIP) has recently been recognized as an immune-mediated disease of the pancreas with distinct features (1). It is a rare disease with an annual incidence of ~3.1/100,000, which varies substantially between geographical regions (2). To date, two types of autoimmune pancreatitis have been described (1). Type 1 AIP is the pancreatic manifestation of IgG4-related disease (IgG4-RD). It shares clinical and histological hallmarks with IgG4-RD, namely increased serum Immunoglobulin G4 (IgG4) levels, dense storiform fibrosis, and IgG4-positive plasma cell infiltration of the affected organ (3). Type 2 AIP is known as idiopathic duct-centric pancreatitis and is characterized by neutrophil-mediated duct destruction, in the form of granulocytic epithelial lesions (GEL) (4). Both types can cause abdominal pain and jaundice and can ultimately lead to chronic pancreatitis (1). This in turn, might even increase the risk of developing pancreatic cancer (5). Yet, the incidence of these complications has not been clearly established.

In the last two decades, several efforts have been made to establish diagnostic criteria (1, 6–8), which are all based on the combination of clinical, serological, and pathological features. Nevertheless, AIP cases are still missed or even mistaken for pancreatic ductal adenocarcinoma (9, 10). As such, sequelae of chronic pancreatitis with endocrine and exocrine insufficiency can develop or the diagnosis of type 1 and type 2 AIP is made after unnecessary surgery (11). In addition, a discrete percentage of AIP cases does not fulfill diagnostic criteria for type 1 or type 2 AIP and thus are referred to as Not-Otherwise-Specified (NOS) AIP (1).

All AIP subtypes respond dramatically to steroid treatment (up to 99% in the different cohorts) (11–14), but the optimal dose to induce remission remains controversial. Reported induction doses have ranges between 30 and 60 mg daily (11–14) Recently, other therapeutic options, that induce B-cell depletion, have also been employed in inducing AIP remission, with promising results (15, 16). In a cohort from France, the reported efficacy was 94% with two infusions given in most patients (17). However, in spite of the dramatic response to initial treatment, the risk of relapse within 1 year from disease remission ranges between 30 and 50% (12), being higher in type 1 than in type 2 AIP patients (12). Several risk factors for AIP relapse have been proposed, but have not been validated prospectively (11, 12, 18, 19). Due to the high frequency of relapse after induction, some authors recommend maintenance treatment with low-dose steroids or immunomodulators, but the patient group that would benefit from maintenance is currently unknown (20–26).

Thus far, data on the epidemiology and natural history of AIP are still scant due to its rarity and its relatively recent appraisal. Most of the data comes from Asian or North-American cohorts, while data on large European cohorts are lacking. As a consequence, treatment options applied in Europe are largely based on retrospective studies from Asian and North-American patients.

We established the PrescrAIP (A Pan-European Study on Current Treatment Regimens of Auto-immune Pancreatitis) study network to retrospectively describe the current status of AIP treatment in Europe on a large scale. In addition, our effort will create the opportunity for a subsequent international prospective registry that will be able to provide definite answers in the future. In particular, in this retrospective multicentre study, we aim to define and compare the AIP treatment regimens used throughout different European centers, highlighting their differential impact on disease remission and long-term outcomes. These results will foster our knowledge of this rare disease, yielding to better patient care.

## Objectives

The primary objective of this study is to describe AIP treatment regimens across Europe, and to compare the effectiveness of treatment regimens in inducing remission, preventing and treating relapse. The secondary objectives include identifying risk factors for relapse, assessing the diagnostic accuracy of the U-AIP criteria (6), assessing the performance of the M-ANNHEIM score for predicting relapse (19), and assessing long-term outcomes including pancreatic exocrine insufficiency and pancreatic cancer. Thirdly, we are aiming to assess whether standard treatment was altered due to pre-existing diabetes mellitus, determine the prevalence of diabetes mellitus before and after steroid treatment, assess glycemic control in patients with diabetes mellitus and to describe the clinical, radiological and pathological characteristics of a cohort of patients diagnosed with AIP through pancreatic resection.

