## Methods

### Study Design

This is an international, retrospective, observational cohort study including all AIP patients. We used the Pancreas2000 framework (www.pancreas2000.org) to create a study network starting with the six centers in the PrescrAIP core group. Additional European centers with expertise in the treatment of AIP patients have been recruited, accumulating to a total of 44 collaborating centers.

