### Study Population

Every patient with an AIP diagnosis (type 1, type 2 or NOS-AIP) will be included, regardless of diagnostic criteria used (U-AIP, HISORt, ICDC). Patients with AIP diagnosed prior to 2005 will be excluded due to lack of uniformity in diagnostic standards.

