### Study Endpoints

Our primary endpoints consist of remission of disease (defined as the absence of clinical symptoms and the resolution of pancreatic abnormalities on imaging), relapse of disease, relapse rates compared between patients with a low or a high dose regimen, cumulative maintenance therapy dose and relapse-free survival time. Our secondary study endpoints are gold standard diagnostic tools of AIP compared to U-AIP, the prevalence of pancreatic exocrine insufficiency and the cumulative incidence of pancreatic ductal adenocarcinoma. The diagnosis of diabetes mellitus [as defined by the American Diabetes Association (27)] either before or after steroid treatment is our tertiary study endpoint.

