### Statistical Analysis

Continuous, non-normally distributed values will be presented as median and interquartile range (IQR), unless otherwise specified. Discrete variables will be presented as frequency (percentage). Normal distribution of continuous variables will be assessed with the Kolmogorov–Smirnov algorithm. Normally distributed variables among the different groups will be compared using the Student's *t*-test. Non-normally distributed variables will be compared using the Mann–Whitney *U*-test. Categorical variables will be analyzed by the Fisher's exact test or chi-square test.

To compare remission rates, relapse rates, relapse-free survival and long-term outcomes between participants, we will stratify participants according to the date of diagnosis, meeting the different diagnostic criteria, the type of treatment, the glucocorticoids starting dose, the cumulative dose, tapering speed, and treatment with maintenance treatment.

Moreover, to assess the impact of the treatment effect being part of the diagnostic criteria, we will perform sensitivity analyses comparing the study outcomes between those classified as AIP regardless of the steroid trial, and those in whom the diagnosis was dependent on the steroid trial. Sensitivity analyses will also be performed to compare the study outcomes including or excluding individuals that do not meet any available diagnostic criteria, and those classified as NOS-AIP.

Kaplan-Meier curves will be used to assess time-to-relapse. Time-to-relapse will be compared between subgroups using the log-rank test. Univariable and multivariable analyses with a backward selection procedure will be performed to identify possible predictors for relapse, based on a Cox-proportional hazards regression model. A significance threshold of *P* < 0.05 will be used.

Data from national pancreatic cancer registries will be used to determine age- and sex-specific incidence rates for pancreatic ductal adenocarcinoma. Standardized incidence ratios (SIRs) will be then calculated by obtaining the ratio of the observed to the expected number of cases, and 95% confidence intervals (95% CIs).

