This project has several strengths. Based on a multicentre cohort, this pan-European AIP study will provide a large dataset, dealt by field experts. Indeed, the vast majority of AIP reports derive from North-American or Asian cohorts, with most likely distinct genetic or environmental features that might not be shared by European AIP patients. Therefore, our study will plausibly provide a more homogenous AIP population thus far not included in recent trials. Due to the rarity of AIP, multicentric collaboration offers the unique possibility of obtaining more reliable results since larger patients' cohort can be analyzed. Moreover, the electronic datasheet will guarantee data quality and safety and will also stimulate data homogeneity across the various very heterogeneous countries and practices.

The study does not come without limitations, it being a descriptive retrospective study. There is a risk of the clinical and diagnostic guidelines being applied differently throughout the recruitment period. To mitigate this, we have collected clinical symptoms, laboratory and radiological findings rather than using the derivative AIP subtyping of the clinician. For example, as in most institutions pancreatic biopsies are not performed, seronegative type 1 AIP confined to the pancreas could be misdiagnosed as type 2. Conversely, atypical type 2 AIP with elevation of serum IgG4 might be classified as type 1 AIP. By subgrouping patients according to clinical, histopathological (where available) and radiological findings we aim to better judge the AIP subtype of the patient we aim to better judge the AIP subtype of the patient and increase transparency and uniformity of the AIP diagnoses made. As the response to a steroid trial might in some cases establish the diagnosis of AIP incorrectly, we will perform a subgroup analysis in patients in whom the AIP diagnosis was based on the successful steroid trial. Hereby, we will be able to estimate the effect of this group on the overall results of our analysis. In addition, we will be enabled to perform sensitivity analyses in that distinct subgroups, as described above. Lastly, many patients have a long follow-up, which should strengthen the true AIP diagnosis.

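### The diagnostic-accuracy objective for U-AIP cannot be met as worded: a cohort of diagnosed AIP patients gives no specificity, and only a possibly inflated sensitivity

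*Protocol article*

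**What the plan says.** The Objectives section of the protocol article names "assessing the diagnostic accuracy of the U-AIP criteria" as a secondary objective, and the Abstract repeats it. Study Endpoints gives the matching endpoint as "gold standard diagnostic tools of AIP compared to U-AIP". The article does not name the gold standard. The full protocol or Appendix 1 may do so, and that gap is not counted as a fault here.

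Study Design describes an "international, retrospective, observational cohort study including all AIP patients". Study Population sets the entry rule: "Every patient with an AIP diagnosis (type 1, type 2 or NOS-AIP) will be included", "regardless of diagnostic criteria used (U-AIP, HISORt, ICDC"). Only diagnoses made before 2005 are excluded. No section describes a group without AIP.

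Statistical Analysis plans robustness analyses of the study outcomes "including or excluding individuals that do not meet any available diagnostic criteria, and those classified as NOS-AIP", and others by whether the diagnosis depended on a steroid trial.

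**The concern.** Diagnostic accuracy describes how well a set of criteria separates patients with a disease from patients without it. That takes both kinds of patient and a reference standard that does not itself rest on the criteria under test. Here the entry rule removes the second kind of patient, and U-AIP is one of the tools by which the first kind was identified.

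If the results are published under an accuracy label, readers will take them as evidence that U-AIP can be relied on to rule AIP in or out. The Discussion concedes that some AIP diagnoses may be wrong: "As the response to a steroid trial might in some cases establish the diagnosis of AIP incorrectly". How often criteria label someone AIP wrongly is a question of specificity, and this cohort cannot answer it. The Introduction also says that AIP cases are still missed or taken for pancreatic cancer. Cases never recognised as AIP cannot enter the cohort, so some of the false negatives are absent as well.

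**Working it through.** The article states no sensitivity, specificity or sample-size figure for this objective, so there is nothing to reproduce. The check is of the 2×2 table, followed by scenarios under assumed values.

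**1. What the table can give.** Take the recorded AIP diagnosis as the reference. Everyone enrolled is diseased, so TN + FP = 0.
- Specificity = TN/(TN + FP) = 0/0, not estimable. Likelihood ratios and AUC need specificity and fall with it.
- Positive predictive value = TP/(TP + FP) = TP/TP = 100%, whatever the criteria do.
- Negative predictive value = TN/(TN + FN) = 0/FN = 0 whenever anyone is U-AIP negative. This too follows from the design and is no estimate of the real quantity.
- Sensitivity = TP/(TP + FN) can be computed.

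Sample size does not enter any of these lines.

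**2. Why the missing specificity matters.** Assume sensitivity 0.90 and 30% AIP among suspected patients. PPV in practice = 0.90×0.30 / [0.90×0.30 + (1 − specificity)×0.70].
- Specificity 0.50: 0.27/(0.27 + 0.35) = 0.44.
- Specificity 0.99: 0.27/(0.27 + 0.007) = 0.97.

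The cohort cannot tell these two apart.

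**3. How far sensitivity could be inflated.** Let s be the true sensitivity and q the share of patients diagnosed by U-AIP. The documents give neither.
- *Worst case.* U-AIP-negative AIP patients at U-AIP-using centres never enter by another route. Observed sensitivity = q + (1 − q)s. With s = 0.80: 0.30 + 0.70×0.80 = 0.86 at q = 30%, and 0.60 + 0.40×0.80 = 0.92 at q = 60%. With s = 0.70: 0.73 at q = 10% and 0.85 at q = 50%. With s = 0.90: 0.91 and 0.95.
- *Intermediate case.* Patients enter if any of the three criteria sets is positive. The other two sets each have an assumed sensitivity of 0.50, independent among true cases. The share missed by all three is 0.20×0.50×0.50 = 0.05, so observed sensitivity = 0.80/0.95 = 0.84. If half of the missed patients enter on clinical diagnosis, it is 0.80/0.975 = 0.82.
- *Complete capture.* Every AIP patient enters by some route. Observed sensitivity = s = 0.80, whatever q is.

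**4. Would dropping patients diagnosed by U-AIP help?** No. It removes only index-positive patients. With complete capture and s = 0.80, the remainder shows (0.80 − 0.30)/0.70 = 0.71 at q = 30% and (0.80 − 0.60)/0.40 = 0.50 at q = 60%. A possible upward bias becomes a downward one.

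**The case against.** The strongest reply is that part of the objective is feasible. Sensitivity is a component of accuracy, and the endpoint is worded as a comparison between diagnostic tools. Assessment Variables records clinical, laboratory and radiological findings and the criteria set used. U-AIP can therefore be re-applied and set against the other criteria. This stands, and the point should not be read as saying that nothing about U-AIP can be learned.

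A reader might also infer that U-AIP positivity is a condition of entry, so that sensitivity is near 100% by design. The documents do not support that. Entry does not depend on which set was used, NOS-AIP is admitted, and Statistical Analysis provides for patients who meet no available criteria. U-AIP is one possible route, and the resulting bias is partial and of unknown size.

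A third reply is that the robustness analyses, or a fuller protocol, take care of it. They do not. Those analyses compare study outcomes with and without certain subgroups, and none supplies verified non-AIP patients. The possibly wrong steroid-trial diagnoses are examined as a subgroup, with no stated procedure for reclassifying anyone as free of AIP. The entry rule itself is stated, and no analysis plan can supply patients whom it leaves out.

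Finally, no section promises that the study will separate AIP from cancer. That remark in the Introduction is background, and this point does not rest on it.

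**Conclusion.** The concern holds in a limited form. Given the stated entry rule, the absence of non-diseased patients is total. Specificity, likelihood ratios and AUC cannot be estimated, and the predictive values are set by the design. This rests on no assumed number.

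Sensitivity is different. It can be reported, and may be too high because of how patients came to be diagnosed. Under an assumed true value of 80%, the scenarios run from no bias to 86% or 92%. The last two are upper-bound scenarios for their assumed q, and it would be wrong to cite them as the expected result.

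The objective should be fixed, but it is secondary. The primary objective on treatment regimens, remission and relapse does not depend on it.

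**What to change.** Reword the objective, in the Abstract and in Objectives, and the matching endpoint as two parts:

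1. The proportion of diagnosed AIP patients who meet U-AIP when it is re-applied to the recorded components. Call it sensitivity only against a named reference standard, for example definitive histology from resection or biopsy. Keep patients whatever criteria set made their diagnosis, and show results by that set. State the remaining incorporation and selection bias. Histology does not remove it, because the Introduction says that all the criteria sets combine clinical, serological and pathological features.
2. Agreement of U-AIP with ICDC and HISORt in the whole cohort, by cross-tabulation and kappa.

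Replace the term diagnostic accuracy and say plainly that specificity cannot be assessed in this cohort. Do not exclude patients diagnosed by U-AIP.

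The cost is mainly wording, since the article already plans to record disease characteristics and the criteria used. The claim becomes narrower. The histology-based estimate will rest on a smaller, selected subset, as the Discussion notes that most institutions do not perform pancreatic biopsies.

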## Methods

### Study Design

This is an international, retrospective, observational cohort study including all AIP patients. We used the Pancreas2000 framework (www.pancreas2000.org) to create a study network starting with the six centers in the PrescrAIP core group. Additional European centers with expertise in the treatment of AIP patients have been recruited, accumulating to a total of 44 collaborating centers.

### Study Population

Every patient with an AIP diagnosis (type 1, type 2 or NOS-AIP) will be included, regardless of diagnostic criteria used (U-AIP, HISORt, ICDC). Patients with AIP diagnosed prior to 2005 will be excluded due to lack of uniformity in diagnostic standards.

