### Setting

The collaboration involves a large number of European centers, most of which are academic hospitals (Figure 1). Starting with the eight centers of the PrescrAIP core group, the study now encompasses centers in Germany (12), the United Kingdom (5), the Netherlands (3), Turkey (3), Italy (3), Spain (3), Norway (2), Poland (2), Russia (2), Hungary (2), Czech Republic (2), Lithuania (1), Ukraine (1), Denmark (1), Sweden (1), and France (1).

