## Discussion

AIP has only been acknowledged as a discrete entity in the last 20 years (1), even though the first reports date back to the 1960's (28). In the last decade, international efforts led to the creation of several sets of diagnostic criteria (1, 6–8), definitely raising awareness on AIP and providing guidelines for its treatment. Despite significant progress in the field, key questions related to the pathophysiology, diagnosis, treatment, and treatment-related complications of AIP remain unanswered. Therefore, AIP still poses a clinical challenge and the diagnosis is still overlooked. In particular, the role and efficacy of glucocorticoids in the induction of remission has been widely accepted and reported, but the optimal starting dose as well as tapering speed is far from being elucidated. In addition, several risk factors for relapse have emerged recently, but only few derive from large cohorts and none have been validated prospectively (11, 12, 18, 19). Finally, long term outcomes in terms of pancreatic exocrine and endocrine dysfunction, as well as incidence rates of malignancies, have rarely been addressed, ultimately impacting on patients' nutritional status and survival (29–31).

To a certain extent, the scarcity of data available can be linked to the low incidence of AIP. Together with its relatively recent appraisal, this complicates the implementation of adequately powered randomized controlled trials. Through an international European-based, multicenter effort, we plan to shed light on this multifaceted condition in order to develop evidence-based treatment strategies in the future. As such, our aim is to collect all available AIP cases, reporting clinical, laboratory, and treatment-related features in order to create an accurate picture of the current European AIP management and to obtain novel data on the natural history of AIP in Europe. Stemming from these, new questions may be formulated and evaluated in a prospective continuation of the present study. In addition, as mentioned above, due to the relatively young age of AIP long-term sequelae have often been overlooked by seminal studies in this field. Yet, a better knowledge in the development of pancreatic exocrine and endocrine (type 3c diabetes or “pancreatogenic” diabetes) insufficiency or treatment related diabetes is warranted in order to deliver better quality of life.

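### Patients who reached an expert centre only after relapse or failed induction elsewhere are eligible and not separated in any listed analysis, so relapse, remission and regimen comparisons may be biased by referral

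*Protocol article*

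**What the plan says.** **Who enters.** Study Population: "Every patient with an AIP diagnosis (type 1, type 2 or NOS-AIP) will be included, regardless of diagnostic criteria used (U-AIP, HISORt, ICDC"). The one exclusion there is: "Patients with AIP diagnosed prior to 2005 will be excluded due to lack of uniformity in diagnostic standards". The Discussion gives the same intent: "our aim is to collect all available AIP cases". Nothing ties entry to diagnosis or first treatment at the participating centre.

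**Where patients come from.** Study Design: "Additional European centers with expertise in the treatment of AIP patients have been recruited, accumulating to a total of 44 collaborating centers". Setting describes the centres as a group "most of which are academic hospitals".

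**What is compared.** Objectives makes the effectiveness of regimens, for remission and for preventing and treating relapse, part of the primary objective. Study Endpoints lists remission, relapse and relapse-free survival time among the primary endpoints.

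**How.** Statistical Analysis: "Kaplan-Meier curves will be used to assess time-to-relapse", with log-rank tests and a Cox model. Its strata are date of diagnosis, diagnostic criteria met, treatment type, glucocorticoid starting dose, cumulative dose, speed of taper and maintenance. The sensitivity analyses there and in Assessment Variables all concern how certain the diagnosis is. The limitations in the Discussion name uneven use of guidelines over time and misclassification of subtype. Place of first treatment, and timing of entry relative to relapse, appear in none of these lists.

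**The concern.** If a patient treated elsewhere comes to an expert centre because the disease has relapsed, the event is the reason the patient is in the cohort. A similar patient treated elsewhere who stayed well is less likely to be seen there. The cohort then holds more relapses than the population it is meant to describe. Entry after failed induction acts on remission in the same way and lowers the observed rate.

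For a purely descriptive rate this is a question of representativeness. For the regimen comparison it can matter more. If regimens started outside the centres differ from those started inside, the outside regimens carry more outcome-selected patients, and a difference can appear between equally effective regimens. This is selection on the outcome, so adjusting for baseline characteristics does not remove it.

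**Working it through.** The article gives no sample size, event count or referral share, so there is no plan figure to reproduce. The calculation shows how large the effect would be under stated assumptions.

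**Inputs.** Unselected relapse risk *p* = 30% to 50%, the one-year range quoted in the Introduction, with 40% as its midpoint. Referral shares, referral ratios and group sizes are all assumptions.

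**1. Pooled relapse.** If a share *f* of the cohort is present only because of relapse, observed relapse = (1 − *f*)·*p* + *f*.

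| *f* (assumed) | true 30% | true 50% |
|---|---|---|
| 0 | 30% | 50% |
| 5% | 0.95 × 0.30 + 0.05 = 33.5% | 0.95 × 0.50 + 0.05 = 52.5% |
| 10% | 0.90 × 0.30 + 0.10 = 37% | 0.90 × 0.50 + 0.10 = 55% |
| 20% | 0.80 × 0.30 + 0.20 = 44% | 0.80 × 0.50 + 0.20 = 60% |

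**2. Regimens started elsewhere.** If relapsers are *r* times as likely to be referred as non-relapsers, observed relapse in patients first treated elsewhere = *pr*/(*pr* + 1 − *p*).
- *r* = 1: no bias.
- *r* = 2: 0.6/1.3 = 46% (true 30%) or 1.0/1.5 = 67% (true 50%).
- *r* = 3: 0.9/1.6 = 56% or 1.5/2.0 = 75%.

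**3. Regimen gap.** Take true relapse of 40% under both regimens, 120 patients per regimen first treated at the centres (48 relapses each), and 60 patients referred at relapse.
- Split 45/15: (48 + 45)/165 = 56.4% against (48 + 15)/135 = 46.7%, a false gap of 9.7 points.
- Split 30/30: (48 + 30)/150 = 52% in both. The level is raised and the gap is zero.

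The gap therefore depends wholly on how unevenly the referred patients fall across regimens.

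**4. Chance of a false P < 0.05.** Suppose 20% of one group, and none of the other, entered because of relapse. The two-sided normal approximation is Φ[(Δ − 1.96·SE₀)/SE₁], with SE₀ pooled and SE₁ unpooled.
- 100 per group, true 30%: Δ = 0.14, SE₀ = √(2 × 0.37 × 0.63/100) = 0.0683, SE₁ = √((0.21 + 0.2464)/100) = 0.0676. The argument is about 0.09, so the probability is about 54%.
- 100 per group, true 50%: Δ = 0.10, SE₀ = 0.0704, SE₁ = 0.0700, so about 29%.
- 200 per group: about 83% and 52%.

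This is the extreme allocation, with all relapse-referred patients in one group.

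**5. Opposite direction.** If a share *g* enters only after passing through the risk period relapse-free, observed relapse = (1 − *g*)·*p*. For *g* = 10% to 20% this gives 27% to 24% (true 30%) or 45% to 40% (true 50%).

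**6. Remission.** The same logic gives (1 − *f*) times the true rate if a share *f* is present because induction failed. The Introduction's figures are for response to treatment, not for remission as Study Endpoints defines it, so only the direction is claimed.

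**The case against.** Most of the case against concerns how far the point can be pushed, and much of it stands.

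- **Relapse rates are inflated.** A reader might infer this as fact. The article never mentions referral and gives no share. Expertise and academic status make relapse-driven referral plausible but do not document it, nor do they show that patients who stay well elsewhere never enter.
- **Regimens given before referral look worse.** This needs both relapse-driven referral and a different regimen mix outside the centres. The Abstract's remark that regimens vary by centre and physician makes a different mix plausible, no more. The even split in step 3 gives no gap.
- **Referred patients are followed from diagnosis or first treatment.** The article states no time origin for relapse and does not say how episodes before referral are handled.
- **Relapse and failed induction act alike.** They do not. Failed induction mainly lowers remission, and such patients may never enter the risk set for relapse.
- **The direction is fixed.** Late entry of relapse-free patients pulls the other way.
- **The material may lie elsewhere.** Appendix 1, which is not shown, holds the full variable list and may already contain the needed fields. Time origin and entry handling are often left to a fuller document.
- **Open eligibility is deliberate.** It suits a rare disease and an objective that includes treating relapse, and the Discussion calls the study descriptive.

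What these do not answer is that the article itself fixes an all-comers population and lists its strata and sensitivity analyses. A referral field in Appendix 1 would go unused by those analyses as written. The descriptive label also does not fit a primary objective that compares the effectiveness of regimens.

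**Conclusion.** The point holds as a risk of unknown size. Eligibility is open to patients first treated elsewhere, and the listed analyses, run as written, would leave any outcome-dependent entry inside the primary comparisons. The more likely result is relapse too high and remission too low, though late entry of relapse-free patients could offset or reverse the effect on relapse.

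Under the assumption that 5% to 20% of the cohort is present only because of relapse, pooled relapse rises by 3.5 to 14 points from a true 30%, and by 2.5 to 10 points from a true 50%. Bias in regimen rankings is conditional: it ranges from none, when referred patients divide evenly, to enough to give frequent false significance when they fall in one group. The article does not allow a choice within that range. The change should be made because it is cheap and because, without the data, the size of the bias cannot be judged afterwards.

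**What to change.** 1. **Data.** Make sure the eCRF holds the place and date of first AIP treatment and the date of first contact with the participating centre, if Appendix 1 does not already include them. This is best settled early: Ethics and Disseminations says data from the German centres (12 of 44 in Setting) are anonymised immediately, so fields not captured at entry may not be recoverable there.

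2. **Analysis set.** Add to Statistical Analysis a prespecified comparison of remission, relapse and relapse-free survival by regimen, restricted to patients whose first AIP treatment was given at a participating centre. Make this the main set for regimen comparison, or at least a planned sensitivity analysis. Define it by place of first treatment. Accepting diagnosis at the centre as an alternative would readmit patients treated elsewhere who relapsed before being diagnosed there.

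3. **Time to relapse.** Where patients first treated elsewhere are kept, start their risk time at first contact and do not count the relapse that preceded or prompted referral. Both parts are needed, because delayed entry alone does not repair entry triggered by the relapse itself.

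4. **Other uses.** Keep all patients for describing regimens and for the treatment of relapse, and report how many were first treated elsewhere.

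The cost is a few chart-based fields, some analysis wording, and fewer patients in the restricted comparison.
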